### **Objective 3 (WP 4 and 5)**

The difference between the inclusion and 18 months of measures from partners' questionnaires will be compared between the three groups. (see Section “*Descriptive analysis*” above for comparative methods).

### **Objective 3bis**

The difference between measures from partners' questionnaires obtained post-intervention (18 months) versus 29 mois +/- 6 mois months later (i.e. 29 mois +/- 6 mois months after the end of the intervention) will be compared between the three groups. (see Section “*Descriptive analysis*” above for comparative methods).

### **Objective 3ter**

The data collected during the qualitative interview on the participant's experience post-intervention will be analyzed.

### **Objective 4 (WP 1 to 6)**

All cognitive measures, psychoaffective measures, life factors, blood, sleep and imaging measures at inclusion will be compared between the group of expert in meditation and the non-expert seniors. (see Section “*Descriptive analysis*” above for comparative methods)

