## 3.3. Provisional schedule of the trial (Flow-Chart)

The projected schedule for the trial is illustrated in Figure 3 below:

Duration of recruitment:

- Non-expert seniors: recruitment will take place 3 months before the beginning of each inclusion wave, i.e. 9 months of recruitment.
- Expert meditators: recruitment will be done on an ongoing basis and over a total period of 73 months (until February 2022; due to an interruption in recruitment in 2020 and part of 2021 linked to COVID-19 and the resulting health measures).

Maximum duration of participation for each participant:

- Expert meditators: 6 months (Screening visit V0 + Inclusion visit V1)

And in the Age-Well substudy - Lockdown: 24 months (April 2020-April 2022)

- Non-expert seniors: 53±6 months (3 months for V0 + V1 + 18 months for intervention + 3 months for Follow-up Visit 3 + 29 months without intervention which is the long-term post-intervention visit (V4)) (± 6 months depending on health status changes and a possible new period of confinement). Total duration of data collection: 6 years (1st participant included in December 2016 and last follow-up of the last participant: in June 2022 ± 6 months depending on the evolution of the health situation and a possible new containment period).

And in the Age-Well substudy - Lockdown: 24 months (April 2020 - April 2022)

Total duration of the research: 7 years (6 years for data collection + 1 year for data analysis) as shown below:

[figure not shown]

Figure 3: Provisional schedule of the Age-Well trial (data collection and analysis).

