#### Study on the expert meditators:

Studies of expert meditators assessing meditation-related changes in brain activity have shown an effect size of  $d=0.74$  (calculated for fMRI change in the insula in response to emotional stimuli; Lutz et al., 2013).

For reasons of recruitment capacity, it was agreed to recruit 30 expert meditators into the trial.

The inclusion of 30 expert meditating participants will allow us to have a power of 95% for the comparison to the 126 non-expert participants, with a first species risk of 5%, to show an effect size of 0.74 in the comparison of brain imaging data.

For the comparison of the 30 expert participants to the 126 non-expert participants, we will have 90% power to show an effect size of 0.67 and 80% power to show an effect size of 0.58, with a two-sided first species risk of 5%.

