## 1. SUMMARY DESCRIPTION OF THE PROJECT

### Scientific background and interest

The coronavirus crisis is forcing us to remain confined to our homes for medical and health reasons. Nevertheless, previous studies have shown negative effects of confinement (recent review in Brooks et al, 2020). And isolation is known to be a risk factor for many psychiatric conditions (Michalska da Rocha et al, 2018; Narita et al, 2020). With the prolongation of the crisis, strict containment measures have evolved into other forms of measures that promote the isolation of populations, especially among the older adults (distancing measures, curfews, etc.). Beyond the containment and distancing measures, the current situation presents a major source of stress and anxiety, all the more worrying as it persists. The Age-Well protocol aims to develop and test approaches to maintain the quality of life of seniors, to preserve their physical and mental conditions and to prevent cognitive decline, dementia, sleep disorders and depression, which increase with age. This project is based on the postulate that mental training in the regulation of stress and emotions through meditation would reduce these effects and thus improve the well-being and mental health of seniors. In this context of deteriorating living conditions, it seems relevant to evaluate how the Age-Well population is affected and reacts to this health situation, and the impact of the mental training tested in the Age-Well clinical trial on the quality of life of seniors during a pandemic.

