A first confinement started on March 17, 2020 in France, and has also started in the USA, where a collaborator has obtained approval for a study on the psychological effects of confinement ([name] in Nashville). We propose to have the participants recruited in the Age-Well trial fill in the questionnaires used in the USA, adapted and translated into French, as soon as we receive the signed consent of the participant (Lockdown Questionnaire n°1), then one month (Lockdown Questionnaire n°2) and 6 months later. This Lockdown Questionnaire n°3, in view of the persistence of the crisis, was proposed during the second national lockdown (announced on October 30, 2020). Three mailings of these questionnaires (Lockdown Questionnaires n°4, 5 and 6) will be proposed again during the different long-term evolution phases of the pandemic (including an evaluation in spring 2021, i.e. ~1 year after the beginning of the pandemic and during the vaccination campaign, an evaluation in the fall of 2021, when the vaccination campaign should be sufficiently underway to signal a gradual return to normalcy, and an evaluation in the spring of 2022, ~2 years after the onset of the pandemic which - ideally - would correspond to a return to normal). The questionnaires will make it possible to evaluate how individual factors (illness, traumatic history, conditions of confinement) modulate the quality of life of seniors during confinement and how the mental training followed modulates this quality of life during confinement.

The funding of this sub-study is ensured by the MMA financing of Lyon and Caen, as well as the financing of the Normandy Label of Excellence Region, which cover the total duration of this sub-study.

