## **2. MATERIEL ET METHODES**

### **A. Participants**

#### **Number of participants:**

We will offer these questionnaires to the 135 seniors and 25 experts included in the Age-Well clinical trial on April 8th, 2020.

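### Objective 4 compares experts and seniors at inclusion with no check on assessment date, although up to 5 of 30 experts may have been assessed during the pandemic and no senior was

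*Combined protocol and SAP*

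**What the plan says.** The secondary SAP, Objective 4, states: "All cognitive measures, psychoaffective measures, life factors, blood, sleep and imaging measures at inclusion will be compared between the group of expert in meditation". The comparator is the non-expert seniors. The section names no calendar-period term, no restriction by assessment date and no sensitivity analysis.

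On timing, protocol section 3.3 gives the span of expert recruitment: "over a total period of 73 months (until February 2022; due to an interruption in recruitment in 2020 and part of 2021 linked to COVID-19". Section 11.2 gives the target: "it was agreed to recruit 30 expert meditators into the trial". The Lockdown sub-study annex (Participants) gives the count reached: "the 135 seniors and 25 experts included in the Age-Well clinical trial on April 8th, 2020". The annex also dates the event ("A first confinement started on March 17, 2020 in France") and describes its likely effect: "the current situation presents a major source of stress and anxiety".

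On adjustment, protocol section 11.3.6 promises adjustment for confounders chosen analysis by analysis, with age, education and gender as examples. The secondary SAP allows covariates where needed. For imaging it lists age, MMSE, sex and education, with AD risk, cardiovascular risk and neuroticism as options. Period is in neither list. Table 5 ticks questionnaires about lockdown periods for experts at V1, but no analysis planned under Objective 4 uses them.

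**The concern.** The two groups were not assessed over the same years. Seniors entered in three early waves, while experts entered one by one over several years, the last of them after the pandemic began. Only experts can have been exposed to the pandemic at inclusion. Covariates such as age, sex and education cannot remove that difference, because they do not carry it.

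Anxiety, depression, loneliness, sleep, activity and stress-related blood markers could all move with the period. A difference on these measures would then reflect partly expertise and partly timing, and the planned analysis could not tell the reader how much of each. The expert comparison is one of the two approaches on which the protocol's rationale rests. The secondary SAP is based on the July and December 2020 protocol versions, so the timing problem could be seen when it was written.

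**Working it through.** **Inputs.**
- Planned experts: 30 (protocol 11.2).
- Included on 8 April 2020: 25 experts and 135 seniors (annex, Participants).
- End of expert recruitment: February 2022 (3.3).
- First participant: December 2016. Last follow-up: June 2022 ± 6 months. Senior participation: 53 ± 6 months (3.3).
- Waves about 6 months apart (6.8). Inclusion visit up to 3 months for seniors and 6 months for experts (6.6).
- First French lockdown: 17 March 2020 (annex).
- Assumption, not in the documents: a pandemic shift of 0.2 to 1.0 SD in the late experts.

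**1. The plan's power figures.** For 30 vs 126 at two-sided 5%, SE = sqrt(1/30 + 1/126) = 0.203 SD. Noncentral t power is 95.1% at 0.74 SD, 90.6% at 0.67 and 81.0% at 0.58. The stated 95%, 90% and 80% reproduce.

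**2. When seniors were assessed.**
- From the waves: December 2016 + 12 months to the third wave + up to 3 months of V1 = about March 2018.
- From the end date: June 2022 − 53 months = January 2018 (July 2017 to July 2018 with ± 6 months).

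Both fall about 20 months or more before 17 March 2020. The count of 135 against a target of 150 does not mean that seniors were still entering. A senior included in April 2020 would finish 53 months later, in September 2024, well past the stated end of data collection.

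**3. How many experts may be late.** 30 − 25 = 5, which is 5/30 = 16.7%. This is a target minus a count. The true number could be lower if the target was missed. It could be higher if some of the 25 were still completing a V1 of up to 6 months on 17 March 2020.

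**4. Which measures.** Those with a V1 value in both groups (Tables 5, 6 and 8) include STAI, GDS, three-item loneliness, PSQI, insomnia severity, cognitive activities, cortisol and CRP. The PSS-14, full UCLA scale and Social Network Index are ticked for experts at V1 but for seniors only at V4. They cannot enter a comparison at inclusion.

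**5. Size of the bias.** Bias in the group difference = (5/30) × shift.

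| Assumed shift (SD) | Bias (SD) | Rejection rate if no expertise effect | Power at 0.58 SD if the shift opposes it |
|---|---|---|---|
| 0 | 0 | 5.0% | 81% |
| 0.2 | 0.03 | 5.3% | 77% |
| 0.5 | 0.08 | 7.0% | 69% |
| 1.0 | 0.17 | 13.0% | 53% |

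The last two columns use the normal approximation with SE 0.203. If 8 of the 30 were affected instead (an illustration), the bias would be 0.05, 0.13 and 0.27 SD.

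**6. Power of a restricted analysis.** For 25 vs 126, SE = sqrt(1/25 + 1/126) = 0.219 SD. Noncentral t power is 91.9% at 0.74 SD, 86.0% at 0.67 and 74.9% at 0.58. The effect detectable with 80% power is (1.960 + 0.842) × 0.219 = 0.61 SD.

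**The case against.** The case for leaving the plan alone has five parts.

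*Size.* Every shift is assumed, and the annex itself expects experts to be only slightly affected. At 0.2 to 0.5 SD the bias of 0.03 to 0.08 SD is well below the standard error of 0.20 SD. This stands and sets the priority. The annex's expectation is, however, a sub-study hypothesis and cannot replace a check.

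*Timing within the pandemic.* Recruitment was interrupted in 2020 and part of 2021, so the late experts probably missed the first lockdown, when disruption was sharpest. This also stands, but the annex still schedules pandemic questionnaires up to spring 2022.

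*Existing provision.* The confounder clause is open-ended, and the lockdown questionnaire supplies data. In principle a period term could be added. Since no senior was exposed at V1, such a term would be estimated from experts alone and would do much the same as restricting by date. The plan permits this but does not specify it.

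*Status.* Objective 4 is observational and sits among the more exploratory objectives (2.2.2). It also compares members of Buddhist centres with seniors from the Caen area, so period is not its only source of confounding. This is correct.

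*Direction.* Because only experts are exposed, a reader might infer that the bias always runs one way or that it flatters the experts. The documents support neither. Who is exposed does not fix the sign, which may differ between anxiety, sleep and activity. If the pandemic worsened the late experts' mood, the bias would work against finding experts better off.

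**Conclusion.** The point holds as a minor one. Senior inclusion visits are all pre-pandemic and some expert visits may not be, yet Objective 4 pools all experts with no check by date. For measures recorded at V1 in both groups, the distortion is one sixth of the pandemic shift if 5 of 30 experts are late: 0.03 to 0.08 SD for shifts of 0.2 to 0.5 SD, and 0.17 SD for a shift of 1 SD. These figures rest on the assumed shifts and on the target of 30 being reached.

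A reader might go further and conclude that five experts were in fact assessed in lockdown conditions, that the perceived-stress comparison is affected, or that Objective 4 cannot be interpreted. The documents support none of these. The number and dates of late assessments are not given, the perceived-stress scale has no senior value at inclusion, and at least five sixths of the planned experts were included by 8 April 2020. The randomised comparisons between the three senior groups do not involve the experts.

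**What to change.** Add to Objective 4 of the secondary SAP:
- The psycho-affective, sleep, lifestyle and stress-related blood comparisons will be repeated with only those experts whose relevant V1 assessment took place before 17 March 2020. The cut is by assessment date, not inclusion date, because an expert's V1 may span 6 months.
- The number of experts assessed on or after that date will be reported for each group of measures.
- The restricted and full estimates will be shown side by side with confidence intervals and judged on direction and size. Significance in the subset will not be required, because the subset has less power and a requirement of that kind could cost more than the bias it guards against.

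The cost is a short addition and one rerun. With about 25 experts, power in the sensitivity analysis is about 92% rather than 95% at 0.74 SD, and 75% rather than 81% at 0.58 SD. It is lower still if fewer than 25 experts were fully assessed before the cut-off. The full analysis is kept unchanged, so it loses nothing.

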### **Objective 5 (WP 1 and 4)**

The main criteria are the fMRI neural activity measured at rest and during the task of SoVT-Rest in meditative states and non-meditative state in the group of experts in meditation.

The different measurement will be compared between mindfulness meditation versus non-meditative state and compassionate meditation versus non-meditative state. (see Section “*Descriptive analysis*” above for comparative methods)

### **Objective 6 (WP 2, 5 and 6)**

To explore associations and/or correlations between psychoaffective measures, life factors and other measures. All statistical analyses of this part will be conducted on the senior non-expert population participants of AGE-Well study at baseline visit (also including data from two other studies when relevant, i.e. SCD-Well and IMAP+).

#### **1. Harmonize and validate the LEQ across countries (PI: [name])**

In a first step (test / construct validity) we will perform multiple regression between LEQ items and items of similar questionnaires expected to measure the same construct (Cognitive Activities Questionnaire and Modifiable Activities Questionnaire). In a second step, we will assess internal consistency reliability using Cronbach's alpha between items expected to measure the same construct (within the questionnaire). Finally, to test for cross-cultural equivalence, we will perform confirmatory factor analyses.

**2. Compare the educational system across countries (PIs: [name]/[name] and [name])**

From the years of education of the participants (from both AGE-Well and SCD-Well), and based on a detailed understanding of the education scheme for each country, we will implement an algorithm allowing to calculate equivalent measures of years of education across countries.

**3. Harmonize and validate the neuropsychological tests and the scale and questionnaires (within and across countries, when relevant) (PIs: [name]/[name] and [name]).** For most tests and questionnaires, especially those that are not standardized, we would need to perform item per item analyses to validate the tests across and within countries. The same procedure as described for the objective a) above will be performed for all tests, scales and questionnaires, when relevant.

**4. Identify the relative relationships between early vs. late life activities and amyloid deposition vs. grey matter (GM) volume (PIs: [name] & [name])**

We hypothesize that higher engagement in cognitive activities will be associated with less amyloid and more grey matter volume; while early versus late life activities would show specific relationships with amyloid deposition vs. grey matter volume.

The relative relationship between early vs. late life activities and amyloid deposition vs. grey matter volume would be measured by LEQ questionnaire, florbetapir-PET and structural MRI, respectively.

Finally, multiple regression analyses, after adjusting for cognitive and emotional scores (MMSE, GDS, IRI) will be performed.

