# 1. RATIONALE FOR THE TRIAL – WORKING HYPOTHESES

The number of people over the age of 65 (referred to as seniors in the following) is steadily increasing in Europe and is expected to rise from 86 million (18% of the population) to about 120 million (24%) in 2040 (Jané-Llopis and Gabilondo, 2008). As the incidence of health problems increases with age, this growth in the number of older people represents a major social and economic challenge for European societies. For example, more than 50% of older adults have sleep problems (Ohayon and Vecchierini, 2005), 10 to 15% suffer from depression (Barua et al., 2011), 7 to 10% develop dementia (Jané-Llopis and Gabilondo, 2008). These health problems are often chronic, require long-term care, and have a significant impact on the quality of life of the individuals, those around them, and on the society in which they live. In addition, these problems are increased by stress and negative emotions, interact with each other, and increase the risk of Alzheimer's disease (AD) (Norton et al., 2014). Numerous studies have shown the deleterious effect of stress on the hippocampus (Ricci et al., 2012), a brain structure important for memory and vulnerable during aging and implicated in AD mechanisms. Sleep disturbances could also accelerate the pathological process of AD (Ju et al., 2013) and each depressive symptom increases the risk of dementia by approximately 20% (Wilson et al., 2002).

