### **1.1.3. Lifestyle**

Various lifestyle characteristics have been widely demonstrated in the literature to have significant and long-term effects on "brain health". Notably, epidemiological studies have shown that

lifestyle has a major effect on cognition in aging and on AD risk (Norton et al., 2014). For example, these studies show that factors, such as physical activity, cognitively stimulating activities, diet, and education level are related to cognitive preservation or decline in older adults, and also to the risk of developing dementia, and specifically AD. **In order to better understand the impact of lifestyle on markers of aging and AD, and to assess whether the effects of meditation could be related to lifestyle changes, different lifestyle measurements will be performed in this study.**

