### **11.3.6. Analysis of the secondary criteria**

The qualitative criteria will be compared between groups by the Chi-square, adjusted Chi-square or Fisher exact test, depending on the expected number of participants under the assumption of independence. Logistic regression models will be used to adjust the comparison for confounding factors where appropriate. The conditions of application of the regression models will be verified.

Quantitative criteria will be compared between groups by Student's t test or Wilcoxon test if the normality of the criterion is not verified. Transformations to normalize the criterion can be performed if necessary. Linear regression models will be used to adjust the comparison on confounding factors if necessary. The conditions of application of the regression models will be verified.

Concerning the imaging data, voxel-to-voxel analyses will be conducted using SPM software, either by using intergroup and intragroup comparison statistics (Two-sample T-test, Full Factorial Design, Flexible Factorial Design... to study differences between different groups at the same visit), and regression (Multiple regression, to study the impact of variables of interest on our measures), or by applying specific and elaborate methods for longitudinal analyses, for which the investigators have developed experience, before performing repeated measures ANOVA. Analyses in regions of interest can also be performed by extracting values (volume, perfusion, amyloid marking, etc.) from the brain maps obtained in the different imaging modalities in order to perform statistical analyses on specific regions.

All analyses will be adjusted for potential confounding factors, which will be identified for each analysis (e.g., age, education level, gender).

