### **6. Identify the relationships between age/AD risk factors and emotions (PI: [name])**

We hypothesize that age and AD risk factors will be associated with changes in emotion measures.

The main objective of this analysis is to determine the effects of AD biomarkers on emotional processing.

For this purpose, functional MRI during emotional task, ageing/AD biomarkers; memory complaints; family background; structural MRI, FDG-PET and AV-45 PET whole brain will be exploited. Correlation analysis and group comparisons will be conducted after adjustment for cognitive and emotional scores (MMSE, GDS, IRI).

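### Objective 6 item 4 tests whether lifetime activity goes with less amyloid and more grey matter, but its only named model conditions on current MMSE, a plausible consequence of both

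*Combined protocol and SAP*

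**What the plan says.** The hypothesis in Objective 6, item 4 is unconditional: "We hypothesize that higher engagement in cognitive activities will be associated with less amyloid and more grey matter volume". Early- and late-life activity, amyloid and grey matter "would be measured by LEQ questionnaire, florbetapir-PET and structural MRI, respectively". The analysis sentence reads: "Finally, multiple regression analyses, after adjusting for cognitive and emotional scores (MMSE, GDS, IRI) will be performed". Item 4 writes out no model without these scores and gives no reason for choosing them.

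The data are cross-sectional: "All statistical analyses of this part will be conducted on the senior non-expert population participants of AGE-Well study at baseline visit". The preamble to Objective 6 also allows two other cohorts to be added where relevant.

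Two general rules apply. Protocol section 11.3.6 says: "All analyses will be adjusted for potential confounding factors, which will be identified for each analysis (e.g., age, education level, gender"). The secondary SAP, under Analysis of imaging data, lists age, MMSE, sex and education as covariates to be used when required. Item 5 of the same objective also concerns amyloid. It first fits a model controlling for age and sex, and adds psychoaffective covariates only in later models.

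**The concern.** MMSE at baseline is measured after most of the lifetime exposure and around the time of the PET scan. Protocol section 1.1.3 says that "cognitively stimulating activities, diet, and education level are related to cognitive preservation or decline in older adults", which puts cognition downstream of activity. Sections 1.1.1 and 1.2.1 describe Alzheimer's disease as bringing cognitive impairment, amyloid accumulation and atrophy, which makes cognition plausibly downstream of the outcomes too.

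If MMSE is a common consequence, conditioning on it links its causes artificially. Among people with equal MMSE, a more active person will tend to carry more amyloid, because something must offset the benefit of activity. The coefficient then answers a different question from the one posed, and it is shifted against the hypothesised sign. The same holds for grey matter if more grey matter raises MMSE. A real protective association could be missed, or a null one reported with the wrong sign. Adding cohorts would not cure this, because the bias does not shrink with sample size.

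**Working it through.** The documents give no effect size, power or sample size for item 4, so there is no figure of theirs to reproduce. The check is of direction and plausible size.

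**Inputs.** n = 135 seniors, from the Lockdown annex, section 2.A. Two-sided 5%, from the secondary SAP's Type I error rate section. True activity-amyloid correlation r = 0 or -0.25, and paths into MMSE of size q = 0.1, 0.2 or 0.3 (positive from activity, negative from amyloid). The correlations and paths are assumptions. Only MMSE is in the calculation.

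**Direction.** With A = activity, Y = amyloid and M = MMSE,

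partial r = (r_AY - r_AM·r_YM) / sqrt[(1 - r_AM²)(1 - r_YM²)].

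If r_AM > 0 and r_YM < 0, the term -r_AM·r_YM is positive and works against a negative r_AY. For grey matter r_AY and r_YM are both positive, so the term is negative and again works against the hypothesis, by the same amount.

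**Size.** With unit variances and M = qA - qY + noise, r_AM = q(1 - r) and r_YM = -q(1 - r). Then

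partial r = [r + q²(1 - r)²] / [1 - q²(1 - r)²].

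The test statistic is approximately z = atanh(partial r)·sqrt(n - 4), with n - 3 when there is no covariate.

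*True r = -0.25.* Unadjusted: atanh(0.25)·sqrt(132) = 0.2554 × 11.489 = 2.934, so power = Φ(2.934 - 1.960) = 83.5%.

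| q | r_AM | partial r | abs(z) | power |
|---|---|---|---|---|
| 0.1 | 0.125 | -0.238 | 2.778 | 79% |
| 0.2 | 0.250 | -0.200 | 2.320 | 64% |
| 0.3 | 0.375 | -0.127 | 1.465 | 31% |

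*True r = 0*, where unadjusted rejection is 5%.

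| q | partial r | z | rejection |
|---|---|---|---|
| 0.1 | +0.010 | 0.116 | 5.2% |
| 0.2 | +0.042 | 0.477 | 7.6% |
| 0.3 | +0.099 | 1.136 | 20.6% |

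At q = 0.3 almost all rejections (20.5 of the 20.6 points) are in the direction opposite to the hypothesis. Simulation agrees: power 31 to 32% and null rejection 21 to 22% at q = 0.3.

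**Reversal.** The sign flips only if r_AM·|r_YM| exceeds |r_AY|. For r = -0.25 both correlations would have to exceed 0.5, that is q > 0.5/1.25 = 0.4. For a weak true correlation of -0.10, MMSE correlations of 0.3 give -0.011 and of 0.4 give +0.071.

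**Screening.** Inclusion requires normal performance on the diagnostic battery (protocol section 4.2.1 and Table 4). I assumed MMSE truncated below -1.65 SD, the cut-off Table 4 sets for two other tests, with a ceiling at +0.5 SD. Adjusted power at q = 0.2 and 0.3 is then about 68% and 40%, and null rejection about 7% and 16%.

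**The case against.** Several points on the other side are sound.

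- **GDS and IRI.** A reader might infer that all three scores are consequences of activity and amyloid. The documents do not support that. Protocol section 1 says that "each depressive symptom increases the risk of dementia by approximately 20" per cent, section 1.2.8 lists depression among dementia risk factors, and item 5 names GDS as a candidate confounder. If GDS affects both activity and amyloid with paths -0.3 and 0.3 and there is no direct link, the crude correlation is -0.09 and adjustment correctly returns 0. Objective 7, item 6 points the other way for emotion in general ("The main objective of this analysis is to determine the effects of AD biomarkers on emotional processing"), so the role of GDS is open. No passage gives IRI a direction. Taking r_AY = -0.20 and an activity-IRI correlation of 0.2, adjustment gives -0.204 if IRI is unrelated to amyloid. It gives -0.25, toward the hypothesis, if IRI also correlates +0.2 with amyloid.
- **Age and sex.** A reader might infer that these are left out. Protocol section 11.3.6 covers them generally, and item 4 merely does not repeat the rule.
- **The word *Finally*.** It may mark a last step after simpler models. None is written, so this remains an ambiguity.
- **The comparator.** Inclusion already conditions on cognition. Under the screening above, the model without MMSE has power of about 81% and 77% at q = 0.2 and 0.3. A harsher screening assumption gave 78% and 68%, and 7.3% null rejection at 0.3. Removing MMSE improves the test without making it clean.
- **Weak paths.** A cognitively normal sample may have paths near 0.1, where little is lost.

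None of these justifies letting the MMSE-conditional model decide an unconditional hypothesis.

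**Conclusion.** The concern holds for MMSE only. The one model named for item 4 conditions on a score that the trial's own rationale makes a plausible consequence of both exposure and outcome, and the resulting bias runs against both parts of the hypothesis. At 135 participants and a true correlation of -0.25, it ranges from slight (about 83% to 79% power) to serious (about 31%) across assumed paths of 0.1 to 0.3. Where the paths truly lie cannot be read from the documents.

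It would go too far to say that the hypothesis is judged wrongly whatever the truth. At modest correlations the effect is attenuation, reversal needs strong paths or a weak true association, and false support for the hypothesis becomes less likely. Protocol section 2.2.2 places Objective 6 among the more exploratory objectives. No intervention comparison or primary result depends on it.

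**What to change.** In Objective 6, item 4, name the deciding model: amyloid or grey matter on LEQ activity, adjusted for age and sex as in item 5 and in line with protocol section 11.3.6, without MMSE, GDS or IRI. Consider education, noting that it may overlap with early-life LEQ. Report the MMSE/GDS/IRI-adjusted model as a labelled sensitivity analysis that does not decide the hypothesis, and state the role assumed for each score. Say also that the optional MMSE covariate under Analysis of imaging data does not apply to the item 4 test. Objective 7, item 6 carries nearly the same adjustment wording and should be checked.

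The cost is a short edit to the SAP, with no new measurements. The downside is that cognition-related recall error in the LEQ, and any confounding by mood, would be handled only in the sensitivity analysis.
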